Since both TCM syndromes and tissue inflammatory cell infiltration are associated with the recurrence rate of CRSwNP, do the characteristics of tissue inflammatory cell infiltration correlate with TCM syndrome types? That is, there are differences in the inflammatory cell infiltration of CRSwNP in different TCM syndrome types, and this difference is a key factor influencing the postoperative recovery of CRSwNP. Hence, we designed a non-randomized, single-center prospective cohort study to explore the correlation among the recurrence rate of CRSwNP and TCM syndrome types and the characteristics of tissue inflammatory cell infiltration. Through this study, we hope to discover a new and simple, effective, and noninvasive way to predict the recurrence rate rapidly after CRSwNP and provide a direction for thinking about the timing of intervention in traditional Chinese medicine, thereby achieving customized diagnosis and treatment, minimizing risks of surgical events, and delaying postoperative recurrence of CRSwNP.

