Deficiency and cold in lung qi	Nasal congestion or light or heavy, decreasing sense of smell, lightheadedness, runny nose which is white and sticky	Onset of sneezing, shortness of breath and fatigue, low faint voice, spontaneous sweating and chills from self	The tongue is pale with thin and white fur, and the pulse is weak and slow	Polyps are white or pale in color and soft
Deficiency and weak in spleen qi	Nasal congestion, decreasing sense of smell, lightheadedness, runny nose, runny or yellow white facies	Weakness and fatigue, eating less, abdominal distension, and loose stools	The tongue is fat with dentate marks, the fur is thin and white or white and greasy or little, and the pulse is wiry and weak	Polyps are white or pale in color and soft

After being included in the study, preoperative data of all participants will be collected, including general information, medical history, TCM syndromes, VAS score of subjective symptoms, Lund-Kennedy score of nasal endoscopy, and CT scan Lund-Mackay score of sinuses. Furthermore, follow-up visits were scheduled at weeks 2 and 4 and months 2, 3, 6, 9, and 12 after surgery, and the subjective symptom VAS score and the Lund-Kennedy score will be also obtained. After the 1-year follow-up, pathological sections of the patients who completed the trial will be obtained, and the infiltration of inflammatory cells will be analyzed under a 400-fold light microscope. Then, the recurrence rate and EOS count percentage of each TCM syndrome type will be applied, and a multiple regression model will be initially established to explore the correlation among postoperative recurrence of CRSwNP and TCM syndrome types and tissue inflammatory cell infiltration types. Finally, we will establish a predictive model for CRSwNP recurrence. The flow chart of the study is presented in Fig. 1. The SPIRIT schedule of enrollment, interventions, and assessments is presented in Fig. 2.

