### Outcome measurements

Our researchers are responsible for follow-up of patients before surgery and at weeks 2 and 4 and months 2, 3, 6, 9, and 12 after surgery. After completing the 1-year follow-up, the recurrence rate will be calculated. Meanwhile, pathological sections of the patients who completed the trial will be analyzed, and the infiltration of inflammatory cells will be visualized under a 400-fold light microscope. All registered patients need to adhere to a 1-year follow-up plan before their data can be used for analysis.

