#### Primary outcome

The primary outcome of this study is to statistically analyze the recurrence rate 1 year after FESS and its correlation with traditional Chinese medicine syndrome types and eosinophil infiltration, in order to establish a predictive model for CRSwNP recurrence.

The definition of recurrence is that mucosal lesions (nasal polyps, mucus purulent discharge, and/or mucosal inflammation and edema) are seen under nasal endoscopy, the symptoms persist for 1 month without any alleviation, and maximum drug treatment is required [22].

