### Statistical analysis

SPSS 23.0 software is used for data analysis.For quantitative data, *t*-test and nonparametric test are used to evaluate the pairwise difference between normally distributed data and non-normally distributed data, respectively. For qualitative data, chi-square test is applied for analysis. *P* < 0.05 is considered statistically significant.Apply logistic regression model to evaluate the relative risk of each variable and its correlation with nasal polyp recurrence.Different traditional Chinese medicine syndromes are entered into a regression model, and the predictive value is determined by the area under the ROC curve (AUC). AUC > 0.9: high predictive value of the model; 0.7 < AUC ≤ 0.9: moderate predictive value. When 0.5 < AUC ≤ 0.7, the optimal diagnostic cut-off point is obtained when the Youden index (sensitivity + specificity − 1) of predictive value is maximized.

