Wen W. et al. have noted that the type of inflammatory-infiltrating cells in polyp tissue directly affects the strategy of postoperative nasal mucosa maintenance medication, which will directly affect the effect of postoperative recovery [27]. Wang Chengshuo et al. have reported that EOS infiltration in nasal mucosa and polyp tissue is closely related to postoperative recurrence. When the EOS ratio is greater than 27%, the probability of postoperative recurrence can be as high as 80%, and the accuracy of EOS in predicting postoperative recurrence can reach as high as 90% [7] . Unfortunately, as predicting recurrence by EOS count is invasive and time-consuming, it is a challenge facing in clinical implementation.

Some studies have indicated that certain differences in postoperative recurrence rates exist among different TCM syndromes of patients [15–18]. Our previous study has found that TCM syndrome type is one of the influencing factors for the postoperative curative effect of CRSwNP, and the type of deficiency and weak in spleen qi had the worst curative benefit. Furthermore, the degree of EOS infiltration differed in the tissues of CRSwNP patients with different TCM syndrome types, and this type presented the highest degree of EOS infiltration [17, 18].

The information obtained from traditional Chinese medicine syndrome differentiation includes symptoms, pulse patterns, and tongue patterns, which are considered subjective. But the use of traditional Chinese medicine syndrome manifestations for clinical prognosis or survival prediction has significant advantages, as it does not require complex and time-consuming laboratory test values.

Corticosteroids are commonly used drugs in postoperative clinical practice for CRSwNP patients. Long-term or short-term hormone therapy can minimize EOS and postoperative recurrence. Chen Jinming et al. have discovered that the cavity accepted CRSwNP surgery with long-acting hormone therapy can effectively reduce the recurrence rate of CRSwNP and improve the cure rate [28]. Wang Chengshuo et al. have also reported that short-term treatment of nasal polyps with budesonide inhalation suspension by nasal atomization inhalation can rapidly improve nasal symptoms and reduce the volume of polyps, implying it can be used as a preoperative endoscopic treatment for EOS CRSwNP patients [29].

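### Syndrome type is put forward as a non-invasive alternative to the eosinophil count, but the stated AUC analysis covers syndrome only and does not show how eosinophils perform in the same patients

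*Protocol article*

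**What the plan says.** The motivation is comparative. The Background states the aim: "we hope to discover a new and simple, effective, and noninvasive way to predict the recurrence rate rapidly after CRSwNP". The Discussion gives the reason for looking beyond eosinophils: "as predicting recurrence by EOS count is invasive and time-consuming, it is a challenge facing in clinical implementation". It also cites a study in other patients in which "the accuracy of EOS in predicting postoperative recurrence can reach as high as 90" per cent.

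Both predictors are in the design. The primary outcome is the one-year recurrence rate and "its correlation with traditional Chinese medicine syndrome types and eosinophil infiltration, in order to establish a predictive model for CRSwNP recurrence". Under Study settings and participants, "a multiple regression model will be initially established to explore the correlation among postoperative recurrence of CRSwNP and TCM syndrome types" and infiltration types, using the EOS count percentage. Under Outcome measurements, "pathological sections of the patients who completed the trial will be analyzed", so EOS will be available for the same completers who supply the recurrence data.

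The Statistical analysis section then describes how prediction is assessed: "Different traditional Chinese medicine syndromes are entered into a regression model", and "the predictive value is determined by the area under the ROC curve (AUC"). An AUC above 0.9 is called high, and one above 0.7 and up to 0.9 is called moderate. EOS is not named in this step.

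**The concern.** If syndrome is attractive because it avoids a biopsy and a cell count, the reader of the results will want to know how much discrimination is given up, or gained, by using it instead. A syndrome AUC judged against absolute bands cannot say. A value near 0.8 earns the moderate label whether EOS in the same patients reaches 0.80 or 0.95.

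The joint regression does not fill the gap. Odds ratios and correlations show that each factor is associated with recurrence. Two factors can both be associated while one discriminates much less well. What is at stake is the interpretation of the predictive model named in the primary outcome; the association aims are unaffected.

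**Working it through.** **1. What the pilot implies for the syndrome AUC.** The inputs are in Sample size calculation: spleen qi 11/26 = 42.3%, damp heat 2/32 = 6.25%, gallbladder heat 0/13 = 0%. These rates reproduce. The groups sum to the stated 71 patients, with 13 recurrences and 58 without. No lung-qi counts are given. The plan states no AUC, so there is none to reproduce.

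*Three-level ordering (spleen qi > damp heat > gallbladder heat):*
- Pairs: 13 × 58 = 754.
- Concordant: 11 × (30 + 13) + 2 × 13 = 473 + 26 = 499.
- Tied: 11 × 15 + 2 × 30 = 165 + 60 = 225.
- AUC = (499 + 225/2) / 754 = 611.5 / 754 = **0.81**.

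*Spleen-qi flag (yes/no):*
- Sensitivity 11/13 = 0.846; specificity 43/58 = 0.741.
- AUC = (0.846 + 0.741) / 2 = **0.79**.

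Both fall in the moderate band. Both are apparent values from the data that set the ordering, so they are likely to be optimistic.

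**2. Whether the cited EOS figure can serve as the comparator.** It cannot. The 90% is an accuracy from other patients, and the documents do not call it an AUC. Accuracy depends on the recurrence rate and the cut-off. In the pilot the spleen-qi flag has accuracy (11 + 43)/71 = 54/71 = 76%, while predicting no recurrence for everyone gives 58/71 = 82%. Setting 76% beside 90% therefore says nothing reliable about the two predictors. Only a comparison within this cohort does.

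**3. How precise a paired comparison would be.**

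Assumptions:
- 200 patients less 10% dropout = 180 completers, all with both measurements.
- Pilot recurrence 13/71 = 18.3%, so m = 33 recurrences and n = 147 without.
- Syndrome AUC 0.80; EOS AUC 0.80 or 0.90. The EOS values are assumptions and are not taken from the documents.
- Correlation r between the two AUC estimates 0 to 0.5.

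Hanley-McNeil variance, with a = A/(2 − A) and b = 2A²/(1 + A):

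Var(A) = [A(1 − A) + (m − 1)(a − A²) + (n − 1)(b − A²)] / (mn)

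- A = 0.80: [0.160 + 32 × 0.0267 + 146 × 0.0711] / 4851 = 0.00235, SE 0.048.
- A = 0.90: [0.090 + 32 × 0.0082 + 146 × 0.0426] / 4851 = 0.00136, SE 0.037.

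SE of the difference = √(V₁ + V₂ − 2r√(V₁V₂)); half-width = 1.96 × SE.

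| Syndrome v EOS | r = 0 | r = 0.3 | r = 0.5 |
|---|---|---|---|
| 0.80 v 0.80 | 0.134 | 0.112 | 0.095 |
| 0.80 v 0.90 | 0.119 | 0.101 | 0.086 |

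The half-width is about **0.09 to 0.13**. For a true 0.80 v 0.90, power to detect the difference is about 50% at r = 0.3 and 63% at r = 0.5. If recurrence were 40% (the 18-month figure cited in the Background; 72 events), the half-width for that pair would be 0.06 to 0.07 at the same correlations.

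**The case against.** The protocol hopes for a non-invasive predictor. It never says that syndrome will match, be non-inferior to or replace EOS. Its stated advantage is convenience, and the Background notes that enough polyp tissue is hard to obtain from a conscious patient. Before surgery the practical alternative may thus be no predictor at all, and an absolute AUC does speak to that use. EOS is also part of the planned modelling, through the primary outcome and the multiple regression. The Statistical analysis section does not say that syndromes are the only variables for which an AUC will be given, and a fuller analysis plan may exist.

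Much of this stands, and it limits the wording. A reader might infer that the protocol promises a substitute as good as EOS; it does not. A reader might also infer from the pilot's 76% and the cited 90% that syndrome has already been shown to be worse; step 2 of the working shows why that does not follow.

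Two parts do not answer the point. The joint regression gives associations, not lost or gained accuracy. And the Statistical analysis section goes beyond a general outline: it fixes what enters the model, the metric, the reading bands and a cut-off rule, and what it fixes is syndrome.

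**Conclusion.** The point holds in limited form. The predictive analysis as written would label syndrome high or moderate without showing how EOS performs in the same patients, although the rationale sets one against the other. The gap is in the stated analysis, not in the data: both predictors are collected in the same completers, so it would be wrong to infer that the study cannot address the question.

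On size, a syndrome AUC near the pilot's apparent 0.79 to 0.81 would be called moderate, and a within-cohort difference from EOS could be estimated to within about ±0.09 to ±0.13. That rests on the assumptions in step 3: completers, pilot event rate, AUCs and correlation. The pilot also lacks one of the four syndrome types.

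It may be tempting to require a formal non-inferiority margin before any favourable statement about syndrome. The numbers do not support that as a requirement. With both AUCs truly 0.80, the expected lower limit is about −0.10 to −0.13, so such a rule would probably be inconclusive at this sample size. The change is worth making before results are seen; it does not call the association aims into question.

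**What to change.** Add to the Statistical analysis section, for completers with both measurements:

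- the AUC with 95% CI of syndrome type, of EOS percentage kept continuous, and of the two together;
- the paired syndrome-minus-EOS difference in AUC with 95% CI, by DeLong or bootstrap;
- a statement that this difference estimates the accuracy gained or lost, and that a non-significant difference will not be read as equivalence.

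The cost is one extra analysis on data already to be collected, with no new visit, assay or patient. The drawbacks are a fairly wide interval at the pilot event rate and, possibly, less favourable wording of the conclusion about syndrome.

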## Discussion

CRSwNP is the chronic inflammatory disease of sinuses and nasal mucosa, accompanied by nasal polyps. FESS has the advantages of surgical precision, small trauma, and removal of diseased tissues while preserving normal tissues and structures, making it the main surgical modality for the clinical treatment of chronic rhinosinusitis-nasal polyps when drug therapy is ineffective. Notably, new lesions developed in the postoperative luminal mucosa transition stage, including secondary infection, mucosal edema, vesicles, and polyp regeneration, are possible important factors of postoperative recurrence.

Whether it is drug therapy or surgical treatment, a scientific method for evaluating efficacy should be based on objective examination results that are compared with the symptoms and signs before treatment. The evaluation of CRS efficacy is divided into two aspects: subjective evaluation and objective evaluation. EPOS2020 [1] and the Chinese Guidelines for the Diagnosis and Treatment of Chronic Nasal Sinusitis (2018) [2] suggest subjective evaluation using the visual analogue scale (VAS) scoring method and objective evaluation using the Lund-Kennedy scoring method for nasal endoscopy and Lund-Mackay scoring method for sinus CT examination. Studies have shown that VAS scores can not only be used to assess the severity of CRS but also guide perioperative management of CRS, thereby better improving the cure rate of CRS [23]. In 1995, Lund and Kennedy proposed the Lund-Kennedy (LK) endoscopic scoring system, which is based on polyps, edema, secretions, scars, and scabs, and have a certain correlation with symptom scores [24, 25]. The Lund-Mackay score is a method of quantifying the severity of chronic sinusitis through sinus CT examination. Through computed tomography, the pathological condition of sinusitis can be more accurately determined [26].

Wen W. et al. have noted that the type of inflammatory-infiltrating cells in polyp tissue directly affects the strategy of postoperative nasal mucosa maintenance medication, which will directly affect the effect of postoperative recovery [27]. Wang Chengshuo et al. have reported that EOS infiltration in nasal mucosa and polyp tissue is closely related to postoperative recurrence. When the EOS ratio is greater than 27%, the probability of postoperative recurrence can be as high as 80%, and the accuracy of EOS in predicting postoperative recurrence can reach as high as 90% [7] . Unfortunately, as predicting recurrence by EOS count is invasive and time-consuming, it is a challenge facing in clinical implementation.

Some studies have indicated that certain differences in postoperative recurrence rates exist among different TCM syndromes of patients [15–18]. Our previous study has found that TCM syndrome type is one of the influencing factors for the postoperative curative effect of CRSwNP, and the type of deficiency and weak in spleen qi had the worst curative benefit. Furthermore, the degree of EOS infiltration differed in the tissues of CRSwNP patients with different TCM syndrome types, and this type presented the highest degree of EOS infiltration [17, 18].

The information obtained from traditional Chinese medicine syndrome differentiation includes symptoms, pulse patterns, and tongue patterns, which are considered subjective. But the use of traditional Chinese medicine syndrome manifestations for clinical prognosis or survival prediction has significant advantages, as it does not require complex and time-consuming laboratory test values.

Corticosteroids are commonly used drugs in postoperative clinical practice for CRSwNP patients. Long-term or short-term hormone therapy can minimize EOS and postoperative recurrence. Chen Jinming et al. have discovered that the cavity accepted CRSwNP surgery with long-acting hormone therapy can effectively reduce the recurrence rate of CRSwNP and improve the cure rate [28]. Wang Chengshuo et al. have also reported that short-term treatment of nasal polyps with budesonide inhalation suspension by nasal atomization inhalation can rapidly improve nasal symptoms and reduce the volume of polyps, implying it can be used as a preoperative endoscopic treatment for EOS CRSwNP patients [29].

However, as a commonly introduced drug in clinic, glucocorticoid is one of the important pathogenic factors of nontraumatic femoral head necrosis [30]. Nasal glucocorticoids may cause side effects, namely epistaxis and perforation of the nasal septum, and the incidence of epistaxis has been reported to be as high as 20% in prolonged use of intranasal hormones over 1 year [31, 32]. However, hormones are an effective but helpless option to reduce the recurrence of CRSwNP and to control symptoms during recurrence.

Numerous studies have shown that the intervention of traditional Chinese medicine in the perioperative period can reduce the postoperative reaction of CRSwNP, minimize the reaction in the postoperative recovery stage, and help recurrence control [33–36]. We assume that the intervention of traditional Chinese medicine after surgery is necessary.

However, in clinical practice, it is very difficult to introduce the intervention of traditional Chinese medicine for every patient after surgery. The reason is mainly due to the economic burden that both patients and surgeons are not able to perform well. After FESS surgery, patients are required to perform postoperative endoscopic examination for about 1 year. Patients whose symptoms are not controlled or partially controlled need a longer period of drug treatment. If the intervention of traditional Chinese medicine is introduced at the same time, the patient is under an increased economic stress, thus leading to lower patient compliance. Meanwhile, as surgeons do not have an accurate prediction on which TCM syndrome type is likely or inevitably to relapse after surgery, they will also take into account the uncertainty in the ratio of the patient’s economic cost to benefit when prescribing traditional Chinese medicine. Consequently, the suggestions for Chinese medicine intervention treatment are discontinued.

The current study is expected to identify that patients with a certain type of TCM syndrome are more likely or inevitably to relapse after FESS, and it is related to EOS, which has currently been explored more frequently than others, hoping to discover a new, effective, noninvasive, and fast way to predict the recurrence rate after CRSwNP as simple as possible. Taking this as a starting point, targeted traditional Chinese medicine intervention is carried out in the perioperative period as a synergistic means of hormone therapy; Moreover, while reducing unnecessary waste of medical resources, it strengthens the confidence of patients and medical staff in introducing the application of traditional Chinese medicine intervention.

Taken together, we prospectively investigated the correlation between recurrence and TCM syndrome types and tissue inflammatory cell infiltration types by exploring the TCM and Western medicine factors of CRSwNP recurrence. The results of the current trial might be helpful for the discovery of a new, effective, noninvasive, simple, and rapid way to predict the recurrence rate after CRSwNP and provide support for integrated traditional Chinese and Western medicine treatment against CRSwNP. The possibility of this study suggested that as a synergistic means of hormone therapy, targeted TCM intervention in the perioperative period might reduce the recurrence rate after CRSwNP surgery, improve the symptoms of patients and their quality of life, and minimize subsequent burdens on the society and economy.

Although the study is observational, it basically adheres to the Standard Protocol Items: Recommendations for Interventional Trials (SPIRIT) statement.

## Data Availability

No data are available.

## Abbreviations

AE: Adverse event
AUC: Area under curve
CRSwNP: Chronic rhinosinusitis with nasal polyps
CT: Computed tomography
EOS: Eosinophil
EOPS: The European Position Paper on Rhinosinusitis and Nasal Polyps
FESS: Functional endoscopic sinus surgery
ROC: Receiver operating characteristic curve
TCM: Traditional Chinese Medicine
VAS: Visual analogue scale
